### Plan for Handling Missing Data

We expect that study participants may drop out or miss visits, thus producing missing data and compromising the ability to conduct an intent-to-treat analysis and draw conclusions about the causal link between the method of monitoring and medication adherence. Since there is no universal method of analyzing missing data [39,40], we will follow the guidelines of the National Research Council (NRC) on the handling of missing data in clinical trials [41]. We will focus on 2 critical elements: (1) careful conduct of the study to limit the amount of missing data, and (2) analysis that makes full use of information on all randomized participants. Careful attention will be paid to assumptions about the nature of the missing data underlying estimates of treatment effects. We will use approaches identified by Little and Rubin [42,43] based on 3 categories for classifying how missing data are generated: missing completely at random (MCAR), missing at random (MAR), and missing not at random (MNAR).

### Data and Safety Monitoring

Since this pilot RCT study employs a low-risk intervention, is not blinded, and does not involve vulnerable populations, we plan to perform a limited scope of data and safety monitoring. The main focus will be on the safe execution of the study protocol as planned [44]. The principal investigators and co-investigators of the study have constituted an independent data monitoring committee to ensure that the trial is conducted according to the approved protocol, including participant recruitment, accrual and retention, participant risk versus benefit, adverse events, periodic assessments of data quality, timeliness, and other factors that may affect study outcomes. All adverse events will be reported to the University of Georgia Institutional Review Board and the Makerere School of Public Health Research Ethics Committee. Summary reports of adverse events will be made to the National Institutes of Health (NIH) in the progress report at the end of month 4, 6, and the final report, unless the nature of a particular event warrants reporting to NIH immediately.

Interim monitoring will be performed after enrolling 50% (36/72) of patients in the VDOT intervention and control groups. This will be done to ensure that the study is conducted according to the protocol and also to check on the level of adherence in both study groups. All analyses will be led by the study biostatistician. Stopping rules will not be applied to this pilot RCT because there is no evidence to inform the threshold for the clinically important difference (ie, the minimum magnitude of the treatment benefit large enough to offset the treatment harms) [44,45]. Stopping the trial would be justified only on the basis of strong evidence of net benefit or harm [45], conditions which are rarely met in small pilot trials like our study.

### Plans for Collecting, Assessing, Reporting, and Managing Solicited and Spontaneously Reported Adverse Events and Other Unintended Effects of Trial Interventions or Trial Conduct

An adverse event in this study is any untoward medical occurrence in a patient that is temporally related to the research, whether or not it is related to the intervention or the patient's participation in the research. Data on all adverse events will be collected after informed consent has been provided and patients have been enrolled in the study. This will continue throughout the study. If a patient experiences an adverse event after providing informed consent but has not started to receive the study intervention, the event will be reported as not related to the study intervention. An adverse event that meets the criteria for a serious adverse event between study enrolment and the end of the study will be reported to the local institutional review board as a serious adverse event.

A serious adverse event for this study is any untoward medical occurrence that is believed by the investigators to be causally related to the study drug and either results in death, is life-threatening, results in severe or permanent disability, requires inpatient hospitalization, or is a significant hazard as determined by the data monitoring committee. Serious adverse events that occur after a patient is discontinued from the study will not be reported unless the investigators believe the event may have been caused by a study intervention or protocol procedure. This will be determined based on a temporal relationship to the study intervention and whether the event is unexpected or unexplained given the patient’s clinical course, previous medical conditions, and concomitant medications.

Potential serious adverse events will include lost to follow-up, death from tuberculosis, data security breaches, violence toward study personnel during patient interaction, complaints about the study from patients, or study clinics. These will be reported to the study coordinator and the study chief investigator, who will look into the matter and discuss it with the affected patient’s case managers, and findings will be reported to the trial steering committee and data monitoring committee.

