**Methods:**

The DOT Selfie study is an open-label, randomized controlled trial (RCT) with 2 parallel groups, in which 144 adult patients with TB aged 18-65 years will be randomly assigned to receive the usual-care DOT monitoring or VDOT as the intervention. The intervention will consist of a smartphone app, a weekly internet subscription, translated text message reminders, and incentives for those who adhere. The participant will use a smartphone to record and send time-stamped encrypted videos showing their daily medication ingestion. This video component will directly substitute the need for daily face-to-face meetings between the health provider and patients. We hypothesize that the VDOT intervention will be more effective because it allows patients to swallow their pills anywhere, anytime. Moreover, patients will receive mobile-phone–based “social bundle” incentives to motivate adherence to continued daily submission of videos to the health system. The health providers will log into a secured computer system to verify treatment adherence, document missed doses, investigate the reasons for missed doses, and follow prespecified protocol measures to re-establish medication adherence. The primary endpoint is the adherence level as measured by the fraction of expected doses observed over the treatment period. The main secondary outcome will be time-to-treatment completion in both groups.

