### Study Procedures

#### Randomization

We will randomize 144 participants with an equal allocation ratio of 1:1 to receive either VDOT or UC-DOT. An equal allocation was chosen to optimize the power of the study [30]. Permuted block randomization with block sizes of 4 and 6 will be used to allocate participants to intervention or control groups while maintaining balance across groups. Each block will have a specified number of randomly ordered treatment assignments [30]. Additionally, stratified randomization will be done according to sex to ensure equal representation of men and women in each study group [30]. The stratification is justified because sex is an important variable that influences adherence to TB treatment [31]. A computer program will randomly generate study arm assignments within block sizes of 4 and 6. This randomization will minimize the likelihood that the study team will be able to predict the next study arm assignment. Each block will contain equal proportions of control and intervention. Within each block will be 4 or 6 sealed, opaque allocation envelopes, depending on the block size. Blocks and allocation envelopes will be sequentially numbered according to the computer-generated randomization schedule. Each allocation envelope will contain an assignment card on which the study group assignment (UC-DOT or VDOT) will be printed. To assign a patient to a study group, blocks will be selected in their sequential order. Allocation envelopes within them will be selected sequentially as well. Each envelope will be opened only after the participant details have been written on it. Carbon paper inside the envelope will transfer participants’ details to the assignment card. Allocation envelopes will be sealed using tamper-proof security tape.

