#### Intervention: Asynchronous Video Directly Observed Therapy (VDOT)

Upon assignment to the intervention study group, participants will receive detailed training (in English or Luganda) on the VDOT app using a training manual provided by the VDOT software developer. The asynchronous VDOT intervention comprises a smartphone with a SIM card, the preloaded VDOT app, a free weekly internet data subscription of 350 MBs paid for by the study at commercial rates, and daily SMS text message medication reminders. The VDOT app is a free downloadable app through the App Store, and the system is Health Insurance Portability and Accountability Act (HIPAA)-compliant and has been validated [33]. Additionally, patients will receive a weekly incentive in the form of social bundles or airtime minutes each time they successfully submit videos for 7 consecutive days. The smartphone will have a unique phone number to ensure that SMS reminders and other phone communications are sent specifically to study participants. The VDOT app is free and downloadable from the Play Store. A unique personal identification number (PIN) will be assigned to each person at registration in the VDOT system to facilitate login into the VDOT app. The PIN will be a security feature that will prevent nonstudy participants, such as other family members or friends, from accessing the app. The app is equipped with video recording features that allow patients to record videos of themselves swallowing pills 7 days each week (Figure 2). To ensure safety and to address concerns that side effects may be missed with limited face-to-face contact, patients are also encouraged to report any adverse events on the daily videos. After the recording ends, an automatic, encrypted, time-stamped video is transferred through a cellular connection and uploaded to a secure cloud server for storage and playback. This enables patients to securely and confidentially record and submit daily medication doses. Once a submission is completed, the patient cannot retrieve or access the video. The smartphone will automatically receive the internet bundles to facilitate video submission.

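### The serious adverse event definition requires causation by a study drug that the trial does not have, and it conflicts with the list of potential serious events that follows it

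*Protocol article*

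**What the plan says.** All the safety definitions stand in one section of the protocol article, Plans for Collecting, Assessing, Reporting, and Managing Adverse Events.

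- **Adverse event.** An untoward medical occurrence that is "temporally related to the research, whether or not it is related to the intervention". Collection runs from consent and enrolment to the end of the study.
- **Serious adverse event.** "any untoward medical occurrence that is believed by the investigators to be causally related to the study drug". The event must in addition meet one of five seriousness criteria: a fatal outcome, a threat to life, lasting or severe disability, admission to hospital, or a hazard that the data monitoring committee judges significant. Events that meet this definition go to the local institutional review board as SAEs.
- **After discontinuation.** SAEs are not reported unless investigators think that the intervention or a procedure of the protocol may have caused them.
- **List.** "Potential serious adverse events will include lost to follow-up, death from tuberculosis, data security breaches, violence toward study personnel during patient interaction, complaints" (from patients or clinics). These go to the coordinator and chief investigator for review, and findings go on to the steering and data monitoring committees.

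The Randomization section states what is compared: "We will randomize 144 participants with an equal allocation ratio of 1:1 to receive either VDOT or UC-DOT". The intervention section describes its content: "The asynchronous VDOT intervention comprises a smartphone with a SIM card, the preloaded VDOT app, a free weekly internet data subscription", with text reminders and incentives. TB treatment is routine care in both arms.

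**The concern.** An SAE definition should sort events by how serious they are, with cause judged separately. Here cause is part of the definition, and the cause named is a drug that the trial does not test. The list in the next paragraph then names events that cannot satisfy the definition. Staff who classify a death or an admission therefore have two rules that give different answers.

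What is at stake is the SAE label, the SAE report to the local board, and any comparison of SAEs between arms. The occurrence of adverse events is among the trial's listed outcomes, and the trial replaces much in-person observation with video, so an SAE count that means the same thing in both arms is worth having.

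**Working it through.** The article gives no figure for this point, so no arithmetic applies. The check takes event types one at a time and puts them through each statement as written.

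| Event | Adverse event definition | SAE definition, read literally | Potential-SAE list |
|---|---|---|---|
| Death from TB | Yes | No: not a drug effect | Named |
| Death from another cause, not attributed to a drug | Yes | No | Not named |
| Hospital admission not attributed to a drug | Yes | No | Not named |
| Hazard identified by the data monitoring committee, not attributed to a drug | Yes, if a medical occurrence | No: the causation condition also governs this criterion | Not named |
| Serious reaction attributed to the TB medicines | Yes | Unclear: yes only if the routine regimen is meant by study drug | Not named |
| Loss to follow-up | No: not a medical occurrence in itself | No | Named |
| Data breach, violence toward staff, complaint | Mostly not medical occurrences | No | Named |

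Four things follow.

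1. **The causal agent is missing.** Neither arm is assigned a drug, and the article never calls the TB regimen a study drug.
2. **The causal agent changes within the section.** The definition names a drug. The rule for events after discontinuation names the intervention or a procedure. The rule for events between consent and the start of the intervention also speaks of relation to the intervention.
3. **The definition and the list do not meet.** No listed item satisfies the definition as it stands. TB death is the clearest case: it is a medical occurrence and fatal, yet it fails on cause. The text gives no rule for when a potential SAE becomes an SAE.
4. **The consequence is one of class.** A death or admission not attributed to a drug remains an adverse event. It loses SAE status and the SAE report to the local board.

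On who decides: the definition turns on what investigators believe. The Blinding section says that participants, research nurses and interviewers cannot be blinded, and that the data collection tools make the arm obvious. The information on which cause is judged therefore comes from people who know the allocation.

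**The case against.** The best defence is that little is lost in practice. All adverse events are collected whether related or not. The Data and Safety Monitoring section sends all of them to both ethics boards, summarizes them for the funder with immediate reporting where an event warrants it, and puts adverse events in the data monitoring committee's remit. TB deaths have a route of their own to both committees. This stands. A reader might infer that serious events go missing, but the documents do not support that: the events are misclassified, not lost.

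Other stronger readings also fail.

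- *Every listed item is tallied as an SAE, so the committee sees mainly retention failures.* The list says potential, has its own review route, and describes no tally. Applying the 14% attrition allowance to 144 participants does not size the problem either. It is a deliberately high planning allowance for all attrition, while loss to follow-up is defined separately as no return for two consecutive months.
- *The adverse event definition conflicts with the SAE definition.* A broad class without a causal condition and a narrower subset with one are compatible. The conflict is between the SAE definition and the list.
- *No event could ever qualify.* If study drug was loosely meant as the TB regimen, serious drug reactions would qualify. Deaths and admissions from the disease itself still would not.
- *The plan itself warns of missed deterioration under video observation.* The concern it states is missed side effects, which it addresses by asking patients to report adverse events on the daily videos.

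The Blinding section also says that study investigators are blinded to allocation, which would limit bias in their judgement if it holds. It does not remove the problem, because the staff who supply the information are unblinded.

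**Conclusion.** The point holds as an internal contradiction in the safety definitions. The SAE definition depends on a study drug that does not exist in this trial, the section uses a different causal agent elsewhere, and the list of potential SAEs cannot be squared with the definition. Followed as written, deaths and admissions not attributed to a drug are reported as adverse events but not as SAEs. Because that class depends on a causal belief in an open-label trial, SAE counts by arm would not be interpretable.

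The size cannot be put as a number: the article gives no expected rate of deaths or admissions and no rule for counting the listed items. The defect is confined to safety classification and reporting. The primary outcome, its test and the sample size do not depend on it, and no stopping rule uses SAE counts. The conclusion assumes only that the definition is applied literally. The looser reading of study drug narrows the problem but does not remove it.

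**What to change.** Reconcile the definition and the list.

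1. Define an SAE by seriousness alone, regardless of cause, and remove the reference to a study drug.
2. Record relatedness to the study intervention or study procedures as a separate field on the case report form, and use the same causal agent in the rule for events after discontinuation.
3. Move loss to follow-up, data breaches, violence and complaints to a separate list of reportable incidents, keeping the review route already described. A TB death then qualifies as an SAE through its seriousness and needs no special listing.

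The cost is wording in the protocol, a change to the form, and a few more SAE reports to the local board.

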## Results

The study was funded in July 2019 and has been approved by the institutional review boards of the University of Georgia (November 12, 2019) and Makerere University (February 26, 2020). Due to the COVID-19 pandemic, study enrollment was delayed for 4 months. Participant enrollment into the RCT began in July and will continue through November 2020. Follow-up will continue through June 2021, when data collection is expected to be completed. Analysis, interpretation, and preliminary dissemination of results are planned for June 2021 to August 2021, through local workshops and scientific conferences. The main results are expected to be published by December 2021. Since the study is being conducted during the ongoing COVD-19 pandemic, there might be unintended negative impacts on the delivery of usual care with DOT. Access to treatment for people with TB is likely to be interrupted as community health workers, doctors, and laboratories devote their energies and resources to the COVID-19 response. There is a potential risk that prevention and treatment programs for the existing conditions will be disrupted. Although such disruptions could inflate the effectiveness of VDOT given that the technology use limits in-person contact, we can only speculate on the magnitude of this effect. The degree to which study findings will be generalizable to nonpandemic times may also be altered. To address some of these concerns, questions related to the impact of COVID-19 on access to routine TB services have been included in the baseline and follow-up questionnaires. This will facilitate further interpretation of the results in the context of prevailing circumstances. Separate studies are needed to evaluate the impact of COVID-19 on the health system and patient care.

## Discussion

### Rationale

Nonadherence to treatment in patients with TB is a serious obstacle to the realization of the World Health Organization’s End TB Strategy goals [46] because it is responsible for the emergence of multidrug resistance and prolonged periods of infectiousness [4,47]*.* Currently, there is a lack of universally feasible, acceptable, and effective strategies to monitor and support adherence to TB treatment. This creates a critical need to evaluate VDOT applications under more diverse conditions and settings to define their function and compare them with traditional approaches to treatment monitoring [48,49]. Mounting evidence suggests increased utility and effectiveness of accessible mobile technologies in enhancing the monitoring of patients with chronic diseases [48-50]. The increased utility can be attributed to the increasing affordability and reliability of smartphones in both high- and low-income settings, while the expansion of cellular and internet networks in developing countries is responsible for the effectiveness of mHealth technologies. Therefore, VDOT is a promising alternative way to mitigate the adverse impact of nonadherence on individuals, families, and communities, especially in underserved populations in Africa.

### Ethical Implications

As it is currently practiced in Uganda, in-person DOT has the potential to be stigmatizing for patients, as it may result in unwanted public disclosure of patient disease status. This fear of—or reality of—stigmatization can negatively impact patient autonomy in regard to treatment-seeking behavior and treatment adherence [51]. However, mHealth technologies such as VDOT are likely to be less stigmatizing as they do not require health workers to visit patients at home or work. The remote nature of interaction minimizes the chances of unintended exposure of private information. The flexibility of making video recordings at the patient’s desired time and place greatly enhances privacy [46]. Patients agreed that VDOT promotes autonomy and a sense of control over their health [18]. Nonetheless, even with the use of VDOT, the potential for stigma, unintended disclosure, and a loss of autonomy could still be present given that videos contain identifiable information like the patients’ faces. At the study exit, we will conduct qualitative interviews with study participants selected to discuss their varying experiences with both VDOT and UC-DOT successes, concerns, and failures that may have affected their adherence to treatment during the study.

This protocol describes the design and methods of a randomized control trial assessing the effectiveness of using VDOT plus incentives to improve medication adherence in TB treatment in Uganda. This RCT leverages the accessible features of mobile phone technology to deliver VDOT remotely, in a less intrusive and less cumbersome way, than in-person DOT. It explores a patient-led management approach that is more convenient, enabling patients to take medications on their schedule.

### Strengths in the Context of Prior Work

The proposed study is innovative because it is the first time that an RCT will be conducted to evaluate VDOT in an African setting. The control participants receiving usual-care DOT will provide an important comparison that will enrich our understanding and inform future interventions using VDOT and other mHealth programs. Fundamentally, Kampala, Uganda (the proposed site of the pilot study), has a significantly higher incidence of TB disease (201 cases per 100,000 in 2017) than any of the other locations where VDOT has been evaluated to date [2].

